**Figure 2. F2:**
[figure not shown]
Participant flow across phase 1 (stakeholder sensitization), phase 2 (adolescent sensitization), and phase 3 (product allocation and 12-month follow-up), with enrollment and retention figures updated as of March 2026. ANM: auxiliary nurse midwife; ASHA: accredited social health activist; AWW: Anganwadi worker; FGD: focus group discussion; MC: menstrual cup.

### Theoretical Framework

Intervention content and delivery are underpinned by the COM-B model and Behavior Change Wheel [18], which were selected because they explicitly link behavioral diagnosis (why uptake of MC and MP is currently low) to specific intervention functions (education, persuasion, training, modeling, and enablement) used in this study. Table 1 maps each COM-B component (Capability, Opportunity, and Motivation) to the corresponding intervention activities and outcome measures used in phases 1‐3.

**Table 1. T1:** Mapping of Capability, Opportunity, Motivation–Behavior components to intervention activities and outcome measures.

COM-B^a^ component	Definition	Intervention activities (study phase)	Outcome measures
Capability–psychological	Knowledge and understanding needed to use MCs^b^ and MPs^c^ correctly	Structured training on menstrual physiology, product mechanics, and insertion or removal technique (phase 1 workshops; phase 2 adolescent sessions)	Pre-post knowledge scores (phase 1 and phase 2 questionnaires)
Capability–physical	Practical skill to insert, remove, and maintain the product	Hands-on demonstration using anatomical models; illustrated instructional booklets (phase 1 and phase 2)	Self-reported ease of insertion and removal (acceptability scale, phase 3)
Opportunity–physical	Access to free products, private facilities, and water for cleaning	Free product provision; instructional materials; tracking diaries (phase 3)	Product usage and continuation rates (phase 3 diaries and home visits)
Opportunity–social	Supportive family, peer, and school environment	Single-sex group workshops; guardian information sessions and FGDs^d^ (phase 2 and phase 3)	FGD themes on family or peer support (phase 2 and phase 3 FGDs)
Motivation–reflective	Conscious beliefs, attitudes, and perceived benefits or risks	Myth-busting content and testimonial-based messaging (phase 1 and phase 2 modules)	Attitude subscale scores (phase 1 and phase 2 questionnaires)
Motivation–automatic	Habitual and emotional responses, comfort, and stigma	Peer modeling delivered by trusted community figures (phase 2 sessions; phase 3 follow-up)	Acceptability scale; FGD themes on stigma or comfort (phase 3)

a COM-B: Capability, Opportunity, Motivation–Behavior.

b MC: menstrual cup.

c MP: menstrual panty.

d FGD: focus group discussion.

### Intervention Design and Development

#### Overview

Educational materials for both phases were developed by the study team (comprising public health physicians, a behavioral scientist, and community medicine faculty) through a 3-step process: (1) a rapid review of existing MC and MP education materials and relevant literature to identify core content domains (menstrual physiology, product mechanics, insertion or removal technique, hygiene and storage, and myth-busting); (2) drafting of a stakeholder training module (for phase 1) and a parallel, simplified adolescent-facing module (for phase 2), including presentation slides, an illustrated instructional booklet, insertion or removal demonstration videos using anatomical models, and posters for classroom and community display; and (3) content and face validation by an expert panel of 5 reviewers (2 gynecologists, 1 adolescent health specialist, 1 health educator, and 1 community health worker supervisor), followed by pilot testing of both modules with a convenience sample of 5 community health and education workers and ten adolescent girls (not included in the main study) at a site not used for the main study. Feedback from pilot testing was used to simplify language, add locally relevant illustrations, and adjust session length before finalizing both modules. All materials are available in English, Hindi, and Bengali.

#### Phase 1: Stakeholder Sensitization

##### Workshops

Workshops will be conducted with 40 community health and education workers to build knowledge of menstrual health, sustainable menstrual hygiene practices, MC and MP use, benefits, myths, and insertion and removal demonstrations, using the module described above. A toolkit including information, education, and communication materials, demonstration videos, and posters will be used across 2 half-day workshops per site; the workshops will be delivered by the study team. Pre-post assessments will evaluate changes in knowledge, attitude, and comfort with discussing the topic (see below). Trained community health and education workers will subsequently engage adolescent girls through interactive sessions in schools and community settings using the adolescent-facing module.

##### Presensitization and Postsensitization Assessments

A self-administered, structured questionnaire will be used to elicit information on sociodemographic variables; knowledge of puberty and menstruation; knowledge of menstrual health management; knowledge of sustainable menstrual products (MC, MP), their benefits, and correct use; and attitudes toward the adoption of MCs and panties. The questionnaire is not identical to the instruments used in the cited prior studies [6,24]; rather, it was developed by the study team using selected knowledge-domain and attitude-domain items adapted from those published instruments as a starting point, with the following changes: (1) items specific to the earlier studies’ college and medical-student populations were removed or reworded for an adolescent (grades 8‐12) reading level; (2) items on MPs (not covered in [6,24,25], which addressed MCs only) were newly developed by the study team; and (3) sociodemographic items relevant to this study’s rural and urban Indian sites (eg, school type and residence type) were added. The adapted instrument was pilot-tested for clarity and comprehension among 10 community health and education workers prior to use (Cronbach α for the knowledge subscale was 0.78 in pilot testing). The full study questionnaire (phase 1 stakeholder version and phase 2 adolescent version), with items mapped to their source (adapted vs newly developed), is provided as Multimedia Appendix 1. Feedback will also be collected on the resource materials developed for adolescent girls, to permit iterative refinement before phase 2 roll-out.

### Phase 2: Adolescent Sensitization and Recruitment

The sensitization intervention will be conducted in small-group workshops (approximately 20‐25 girls per group) using materials developed and validated in phase 1, covering menstrual health, hygiene, and correct usage of MCs and MPs. Sessions will be led by previously trained community health and education workers (ASHA, ANM, AWW, and female teachers), ensuring cultural sensitivity and local relevance, and will run for approximately 90 minutes across 2 sessions per group. Adolescents will be recruited as per the inclusion criteria above through school registers (for school-going girls) and community health worker household lists (for out-of-school girls), with information sessions held for parents and guardians prior to enrollment. Preintervention and postintervention questionnaires (structured, self-administered, in the local language) will measure changes in knowledge, attitudes, and perceived readiness to adopt MC and MP, using the same core knowledge and attitude domains as the phase 1 instrument, adapted to the adolescent literacy level. Additionally, 2 focus group discussions (FGDs) will be held at each site—one with adolescent girls and one with their female guardians—to explore barriers and facilitators to product adoption, using a semistructured topic guide based on the COM-B framework (Multimedia Appendix 2). Quantitative data will be analyzed using SPSS (version 26; IBM Corp), and qualitative data will undergo thematic analysis to develop a comprehensive understanding of the social and behavioral influences on sustainable menstrual product adoption.

### Phase 3: Intervention and Follow-up

A total of 416 adolescent girls aged 13‐19 years, equally divided between the 2 study sites, who complete the phase 2 sensitization and provide consent or assent for product use, will be allocated to either of the following:

MC group: receives a size-appropriate medical-grade silicone MC with instructional manual.MP group: receives 3 reusable MPs with instructional pamphlets.

Allocation to the MC or MP group will be based on participant preference following a structured counselling session in which both products, their insertion or use requirements, and maintenance needs are explained; girls who express no strong preference will be allocated using a randomization sequence generated in blocks of 4, stratified by site, to achieve approximately equal group sizes. This preference-informed allocation approach was chosen, rather than full randomization, because acceptability and correct use of MCs in particular are strongly influenced by willingness to use an internally inserted product, and forcing product allocation against strong preference was judged likely to compromise both retention and the validity of acceptability outcomes in a feasibility study of this nature; this deviation from a purely randomized design, and its rationale, is reported here transparently as recommended for feasibility study reporting [20].

Participants will receive free products along with instructional materials and menstrual-tracking diaries that record menstruation dates, school attendance, side effects, and usage challenges. Monthly follow-ups will occur through home visits at 1, 2, 3, 6, 9, and 12 months, conducted by trained community health and education workers using a structured follow-up checklist.

A 12-month follow-up duration was chosen in line with prior longitudinal descriptive work showing that adaptability and correct use of MCs typically stabilize only after several menstrual cycles of sustained use and support [25].

Primary outcomes are product usage, continuation (proportion still using the allocated product at 12 mo), comfort, and acceptability (assessed using a structured acceptability scale administered at 1, 3, 6, and 12 mo, capturing ease of insertion or removal, comfort during daily activities, leakage experience, and overall satisfaction). Secondary outcomes include school absenteeism during menstruation, menstruation-related health complaints, and likelihood of recommending the product to others. FGDs conducted at 6 and 12 months will further explore facilitators and barriers to continued use.

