For the adolescent cohort, assuming a baseline sustainable-product usage rate of 5% and a projected postintervention uptake of 20%, with 80% power and 5% significance, the minimum required sample size was calculated as 304 adolescent girls per site using a standard formula for comparing 2-proportions formula. To account for clustering by school and community catchment, a design effect of 1.5 (based on an assumed intracluster correlation coefficient of 0.02 and an average cluster size of 25 girls, consistent with design effects reported in comparable school-based menstrual health cluster studies) was applied, giving a minimum requirement of 456 adolescent girls per site (total N=912) for the phase 2 sensitization cohort. Of these, a subgroup of 416 girls (n=208 per site) will be enrolled in the phase 3 product-use follow-up; this subgroup size was determined pragmatically in line with recommendations for feasibility and pilot studies, which emphasize that a fully powered comparative sample is not required at this stage but that sample size should still be justified in relation to the primary feasibility objectives (recruitment, retention, and product continuation) rather than a hypothesis-testing end point [22,23]. A minimum of 30‐35 participants per arm per site is considered adequate to estimate continuation and acceptability proportions with reasonable precision (95% CI width ≤±16%) for feasibility purposes, and the planned 203 girls per site substantially exceeds this threshold, allowing additional precision for the secondary comparison between MC and MP users. Twenty community health and education workers per site will be enrolled (total n=40) for training and postintervention assessment; this number reflects the total eligible cadre of ASHAs, ANMs, AWWs, and grade 8‐12 female teachers attached to the selected clusters at each site, and was not derived from a formal power calculation, consistent with standard practice for facilitator and trainer cohorts in implementation feasibility studies.

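### Phase 3 usage, continuation and acceptability are not conditioned on baseline cup or panty use, so existing users can modestly inflate them

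*Protocol article*

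**What the plan says.** **Eligibility.** In Textbox 1 of the protocol article, girls qualify by age, menarche, residence and language. They are excluded for a disability or mental illness that precludes taking part, for pregnancy or lactation, or for lack of assent or consent. The product they use now is not mentioned.

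**Entry to phase 3.** The section Phase 3: Intervention and Follow-up adds only that girls are those "who complete the phase 2 sensitization and provide consent or assent for product use, will be allocated to either of the following", namely the MC and MP groups. Allocation follows the girl's preference. Blocked randomization is used only for girls without a strong one.

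**Assumed baseline use.** Study Flow and Sample Size Calculation plans on "assuming a baseline sustainable-product usage rate of 5% and a projected postintervention uptake of 20%, with 80% power and 5% significance". The Background puts MC and MP uptake in India below 5% in most published reports.

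**Outcomes.** The primary outcomes in the Phase 3 section are product usage, "continuation (proportion still using the allocated product at 12 mo"), comfort and acceptability. None is restricted to girls who were not using either product at baseline.

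**Analysis.** Data Analysis lists the predictors of adoption and continuation as including site, residence type, age, product type, and baseline knowledge and attitude scores. Prior use is not named.

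**The concern.** The Introduction describes an intervention that introduces products few girls use. A girl who already uses a cup has settled on it before the study reaches her. If she chooses the cup, she is counted as continuing at 12 months and rates its ease of use and comfort from experience. The protocol justifies the 12-month follow-up by noting that correct cup use stabilizes only after several cycles, and she has passed that stage. In a model of adoption, she has the outcome before exposure.

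The phase 3 levels have no concurrent group without a product against which prior use would cancel. A mix of new and established users therefore reads as the experience of girls newly given the product, which is what a scale-up decision would draw on. Because allocation follows preference, existing users may also be spread unevenly between MC and MP, and product type is a listed predictor.

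**Working it through.** **Inputs from the protocol article**
- Baseline use 5%; phase 2 cohort 912; phase 3 cohort 416 ("a subgroup of 416 girls (n=208 per site) will be enrolled in the phase 3 product-use follow-up"). The Abstract gives 406, which changes nothing material here.
- Intracluster correlation 0.02 and cluster size 25.
- Allocated so far (Results): 210 of 416, with 104 MC and 106 MP.

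**Assumed, because the article gives no figure:** 12-month continuation in new users (c_new) and in existing users (c_exist).

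**Step 1. The plan's own figures.** The later steps reproduce: 1 + 24 × 0.02 = 1.48, taken as 1.5; 304 × 1.5 = 456 per site; × 2 = 912. The starting 304 per site does not: 5% against 20% at 80% power and two-sided 5% needs 76 per group, and 304 = 4 × 76. That is a separate matter and does not affect this point, which uses only the 5%, the 912 and the 416.

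**Step 2. Expected existing users.**
- Phase 2: 0.05 × 912 = 45.6, about 46.
- Phase 3, entering in proportion: 0.05 × 416 = 20.8, about 21 (20.3 with 406).
- Phase 3, if every one of them entered: 45.6 / 416 = 11.0%.

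**Step 3. Effect on overall continuation.** With w the share of existing users, observed = (1 − w) × c_new + w × c_exist, so the excess over the new-user rate is w × (c_exist − c_new). At w = 5%, in percentage points:

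| c_new | c_exist 100% | c_exist 90% |
|---|---|---|
| 20% | +4.0 | +3.5 |
| 50% | +2.5 | +2.0 |
| 70% | +1.5 | +1.0 |
| 90% | +0.5 | 0 |

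At 95% against 60%: 0.05 × 0.95 + 0.95 × 0.60 = 61.75%, an excess of 1.75 points. With all 46 in phase 3 and all continuing, the excess is 8.8, 5.5, 3.3 and 1.1 points down the rows.

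**Step 4. Effect on the MC-MP contrast.** The shift is (w_MC − w_MP) × (c_exist − c_new). It is zero if existing users split evenly. If all 21 sat in one arm of about 208, w there would be 10%, and at 95% against 60% the shift is 0.10 × 35 = 3.5 points.

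**Step 5. The planned pre-post comparison.** Existing users are in both the 5% and the 20%, so the 15-point change is unaffected. If they all keep using, a level of 20% means that (0.20 − 0.05) / 0.95 = 15.8% of prior non-users took up a product.

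**Step 6. Precision after restriction.** 416 − 21 = 395. The 95% half-width at a proportion of 50% is 1.96 × √(0.25/416) = 4.8 points, against 1.96 × √(0.25/395) = 4.9. With a design effect of 1.48 it is 5.8 against 6.0.

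**The case against.** **The size is small and rests on assumptions.** This stands. The article gives no continuation rates, and 5% is the upper end of its own background figure. An excess of 1.75 points is well inside a half-width of 4.8 and far inside the ±16% tolerance that the article states. Unlike sampling error, though, it is expected to run in one direction, and it can be removed at little cost.

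**Existing users may not choose the product they know.** This also stands. Nothing in the article says what they will choose. A cup user who tries panties and goes back to her cup would count as discontinuing the allocated product. The direction therefore depends on most of them choosing what they already use, which is plausible but not documented.

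**Baseline use may already be recorded.** The adolescent questionnaire is in an appendix not shown, and Data Analysis mentions pre-post practice scores. The predictor list is introduced as non-exhaustive, and fuller detail may lie in an analysis plan. This makes the fix easier. It does not alter the entry rule or the outcome definitions, which the article itself states without reference to prior use.

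**Objective 3 does not say new users.** This is fair: it concerns girls using MCs and MPs over 12 months. Restricting the main result is partly a choice of estimand, but it is the one that matches an intervention meant to bring about uptake.

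**Non-comparable arms are already acknowledged.** Strengths and Limitations notes selection differences between MC and MP groups in general terms. That does not address the absolute levels.

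**Conclusion.** The point holds as a modest bias in the absolute phase 3 results. At 5% existing users, overall 12-month continuation would overstate the new-user rate by roughly 0.5 to 4 points across new-user rates of 90% to 20%, if existing users nearly all continue with the product that they chose. The MC-MP contrast could move by about 3.5 points if they all fall in one arm, which is a worst case.

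Three stronger readings might be inferred, and the documents do not support them:
- **That the planned uptake effect is inflated, with a quarter of the 20% being prior use.** This is true of the level only. Existing users cancel in the change from 5% to 20%.
- **That one phase 3 girl in nine is an existing user.** The 11% figure requires every existing user among 912 girls to take one of 416 places.
- **That the problem runs through the whole study.** Phase 1 enrols only health and education workers, so only phases 2 and 3 are concerned.

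**What to change.** 1. Establish current and past MC/MP use at baseline for each girl. Use the baseline practice items if they capture it. Otherwise add one question, and ask it retrospectively of girls already enrolled, including the 210 already allocated.
2. Define adoption among girls using neither product at baseline, and report the main continuation and acceptability results in that set.
3. Report existing users separately, and add prior use to the continuation model.
4. Leave eligibility unchanged. With 210 of 416 girls allocated, a new criterion would give two differently defined halves. Places might also be hard to fill: 210 of 512 sensitized girls (41%) have entered so far, and that ratio applied to 912 gives about 374, although part of it may reflect timing.

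The cost is about 5% fewer girls in the main analysis set, with almost no loss of precision (Step 6), and reliance on recall for girls already enrolled if the item was not collected.

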### Rigor and Trustworthiness of Qualitative Methods

Qualitative data collection and analysis will follow a reflexive thematic analysis approach as described by Braun and Clarke [26], which emphasizes the researcher’s active, situated role in generating themes rather than treating themes as simply “emerging” from the data. All FGDs will be conducted by 2 trained qualitative researchers (a moderator and a note-taker), audio-recorded with consent, transcribed verbatim, and translated into English where necessary, with back-translation of a 10% sample to check accuracy. Coding will be conducted independently by 2 researchers using NVivo (v14, Lumivero), with a third senior researcher reviewing coding decisions and resolving discrepancies through discussion; reflexive memos will be maintained throughout to document analytic decisions and the researchers’ own positionality (as public health professionals external to the immediate community) and its potential influence on interpretation. Trustworthiness will be addressed using the criteria of credibility (through investigator triangulation, member-checking of preliminary themes with a subset of participants, and prolonged engagement through the 12-month follow-up), dependability (through an audit trail of coding decisions and analytic memos), confirmability (through independent coding and reflexive discussion to limit individual researcher bias), and transferability (through thick description of the study contexts to allow readers to judge applicability to other settings) [27].

### Mixed Methods Integration

Quantitative and qualitative data will be integrated at the design, methods, and interpretation levels using a convergent-parallel mixed methods approach [19]. At the design level, qualitative FGD findings and quantitative questionnaire data are collected concurrently within each phase rather than sequentially. At the methods level, integration will occur through “merging”—quantitative results (eg, proportions reporting continued use and comfort scores) and qualitative themes (eg, reasons for discontinuation and social barriers) will be displayed side-by-side in joint display tables organized by outcome domain (uptake, continuation, comfort or acceptability, and barriers) to identify areas of convergence, divergence, or expansion between the 2 data sources. At the interpretation level, a triangulation protocol will be used in which discrepancies between quantitative and qualitative findings (eg, high self-reported continuation alongside qualitative reports of discomfort) will be explicitly examined and reported rather than resolved by preferring one data source over the other. This directly addresses triangulation as a stated strength of the study design (see Discussion) by specifying, in advance, how it will be operationalized.

